# Personalizing the first dose of FSH for IVF/ICSI patients through machine learning: a non-inferiority study protocol for a multi-center randomized controlled trial

**DOI:** 10.1186/s13063-024-07907-2

**Published:** 2024-01-11

**Keywords:** Controlled ovarian stimulation, FSH, IVF, Machine learning, Decision support system, Artificial intelligence

## Abstract

**Background:**

Adequately selecting the initial follicle-stimulating hormone (FSH) dose during controlled ovarian stimulation (COS) is key for success in assisted reproduction. The objective of COS is to obtain an optimal number of oocytes to increase the chances of achieving a pregnancy, while avoiding complications for the patient. Current clinical protocols do achieve good results for the majority of patients, but further refinements in individualized FSH dosing may reduce the risk of poor ovarian response while also limiting the risk of ovarian hyperstimulation syndrome (OHSS) risk. Models to select the first FSH dose in COS have been presented in literature with promising results. However, most have only been developed and tested in normo-ovulatory women under the age of 40 years.

**Methods:**

This is a randomized, controlled, multicenter, single blinded, clinical trial. This study will be performed in 236 first cycle in vitro fertilization (IVF) and/or ICSI (intracytoplasmic sperm injection) patients, randomized 1:1 in two arms. In the intervention arm, the dose of FSH will be assigned by a machine learning (ML) model called IDoser, while in the control arm, the dose will be determined by the clinician following standard practice. Stratified block randomization will be carried out depending on the patient being classified as expected low responder, high responder, or normo-responder. Patients will complete their participation in the trial once the first embryo transfer result is known. The primary outcome of the study is the number of metaphase II (MII) oocytes retrieved at ovarian pick up (OPU) and the hypothesis of non-inferiority of the intervention arm compared to the control. Secondary outcomes include the number of cycle cancelations (due to low response or no retrieval of mature oocytes), risk of ovarian hyperstimulation syndrome (OHSS), and clinical pregnancy and live birth rates per first transfer.

**Discussion:**

To our knowledge, this is the first randomized trial to test clinical performance of an all-patient inclusive model to select the first dose of FSH for COS. Prospective trials for machine learning (ML) models in healthcare are scarce but necessary for clinical application.

**Trial registration:**

ClinicalTrials.gov, NCT05948293. Registered on 14 July 2023.

**Supplementary information:**

The online version contains supplementary material available at 10.1186/s13063-024-07907-2.

## Administrative information

Note: the numbers in curly brackets in this protocol refer to SPIRIT checklist item numbers. The order of the items has been modified to group similar items (see http://www.equator-network.org/reporting-guidelines/spirit-2013-statement-defining-standard-protocol-items-for-clinical-trials/).

## Introduction

### Background and rationale {6a}

Controlled ovarian stimulation (COS) is a key step for assisted reproduction and fertility treatment. During COS, clinicians prescribe different medications to stimulate the ovaries to produce several mature oocytes [1]. Oocytes are retrieved from the ovaries during the oocyte pickup (OPU) and later fertilized with sperm in the laboratory. Controlling the number of mature or metaphase II (MII) oocytes is critical for success. Ultimately, a higher number of MII oocytes increases the chance of pregnancy [2, 3]. However, treating a patient with the aim of retrieving as many MII oocytes as possible also increases the discomfort and costs of the treatments and the risk of ovarian hyperstimulation syndrome (OHSS), a potentially life-threatening medical condition resulting from an excessive response to stimulating hormones.

The first step in COS involves the selection of an adequate first dose of follicle-stimulating hormone (FSH). This first dose of FSH is important, as it recruits available ovarian follicles to grow. Once follicles are recruited, little can be done to modify the number of oocytes that will be retrieved [2]. A balance must be struck between recovering sufficient mature oocytes to ensure optimal clinical outcomes, while minimizing the risks to the patient. Assigning an appropriate starting dose of FSH thus constitutes an essential clinical decision in the personalization of treatment.

In routine clinical practice, the choice of starting FSH dose is based on patient characteristic, such as her age, body mass index (BMI) and ovarian reserve, amongst others. Yet, despite clinical experience and current evidence-based practice, criteria to accurately select the starting dose of FSH for all patients have not been entirely identified. Accordingly, patients with similar characteristics (or even the same patient treated at different timepoints) may have different, often unexpected, outcomes following the same treatment, possibly displacing them from the optimal range of oocytes (10 to 15 [3, 4]).

Machine learning (ML) models that capture medical experience registered in clinical historical data have been devised in an effort to reduce the extremes of ovarian response and automate the personalization of FSH dose selection. Two good examples include nomograms that use patient age, anti-Müllerian hormone (AMH), or antral follicle count (AFC) and basal endogenous FSH to tailor the first dose of FSH for COS [5, 6]. The nomogram by La Marca et al. (2012) has also been tested prospectively in a randomized controlled trial (RCT) [7]. The authors observed that in the intervention arm, a higher number of patients fell within the optimal range of MII oocytes, while fewer had poor outcomes. Howles et al. developed a model based on multivariate regression [8]. The model was subsequently tested in an RCT study [9]. While similar pregnancy rates were achieved compared to clinical practice, the authors observed a reduction in OHSS cases when using the model. Finally, another randomized trial was performed for a model developed specifically for FSH delta [10]. Dose allocation by the model resulted in more patients within the target response (8–14 oocytes), less excessive responses ($$\ge$$ 15 oocytes in the high AMH stratum), and less poor responses (< 4 oocytes in the low AMH tier), when compared to a non-personalized-dosing control group. However, no differences in pregnancy and live birth rates were observed.

While these approaches report clinically relevant outcomes, they were developed and tested using data from normo-ovulatory patients under the age of 40. Ultimately, patients for whom correct FSH dosing is most critical were excluded. To account for a more comprehensive IVF/ICSI patient population, we developed and trained an inclusive FSH dosing model named IDoser [11].

IDoser includes age, body mass index (BMI), AMH levels, and AFC as predictors. It was developed and trained while incorporating available clinical evidence encoded as rules during parameter optimization. The objective of IDoser is to optimize the number of oocytes retrieved during ART treatment, achieving an appropriate balance defined as 10–15 oocytes, as suggested by literature ([3, 4]). When compared to real-life clinical practice, the IDoser performed significantly better (*p *< 0.05), showing an expected 11.6% increase in the proportion of patients who were closer to the optimal range of oocytes [11, 12]. In this study, we have specifically chosen a non-inferiority trial design with the specific goal of refining and standardizing the FSH dosing model in clinical practice. This approach is fundamentally different from attempting to prove the superiority of the new model. Instead, our focus is on demonstrating that our newly developed FSH dosing model maintains at least the same level of efficacy as the existing clinical standard. Opting for a non-inferiority trial is particularly beneficial in this context, as the current standard for FSH dosing is effective, and our goal is to offer an alternative that provides more standardized dosing guidelines and reduces variability in patient outcomes, particularly in the number of oocytes retrieved, without sacrificing treatment efficacy. By aiming to align closely with the high-quality care standards already in place, this methodology is well-suited to our objectives of enhancing and streamlining the FSH dosing process. Furthermore, the non-inferiority trial’s requirement for a smaller sample size aligns well with the practical constraints of clinical research, making it an appropriate choice for assessing our FSH dosing model.

### Objectives {7}

This RCT tests the hypothesis that the performance of IDoser in prescribing the initial dose of FSH during COS is not inferior to the performance of a clinician in the average number of mature oocytes retrieved. Secondary objectives include the effect of IDoser on number of cycle cancelations (due to low response or no retrieval of oocytes), number of cases with OHSS risk, clinical pregnancy, and live birth per first transfer.

### Trial design {8}

The trial design is a single-blinded RCT with two arms with a 1:1 allocation ratio, comparing outcomes following FSH dose selection by IDoser and dosing based on standard clinical practice.

The hypothesis that will be tested is whether the performance of IDoser selecting the first dose of FSH is non-inferior to the standard clinical protocol in regards to the average number of mature oocytes recovered per group. The difference in the number of MII that is regarded to be clinically significant is 2 MII. Our decision to consider a difference of two MII oocytes as clinically significant is based on empirical evidence and clinical relevance. As only 30 to 40% of inseminated mature oocytes develop into blastocysts [13, 14], the choice of two MIIs strikes a balance between statistical significance and clinical practicality, while taking into account the consequent impact on the success of fertility treatments. If the average number of MII in the intervention group is inferior in 2 or more units, IDoser will be considered inferior to the standard clinical practice.

## Methods: participants, interventions, and outcomes

### Study setting {9}

This is a randomized, single-blinded, multicenter, clinical trial. It will be carried out in two distinct centers in Spain, both of which are part of the same IVF group.

### Eligibility criteria {10}

Eligibility criteria for patient recruitment in this study are rigorously established and will be assessed by the clinician during the pre-treatment consultation. The inclusion criteria for participants are as follows: individuals aged 18 years or older, but not exceed 50 years of age; first autologous conventional IVF and/or ICSI cycles, irrespective of the underlying causes of infertility; the use of FSH on the first day of stimulation (which can be combined with luteinizing hormone, LH). Exclusion criteria include: natural cycles (without COS); and cycles in which FSH is not measured in international units (IU).

### Who will take informed consent? {26a}

Participants will be enrolled in the trial only after receiving comprehensive information about the study, being provided with a written consent form by medical personnel, and formally agreeing to participate by signing the form. They will be informed of the study during by their consulting physician following the recommendation of an IVF/ICSI treatment. Patients considering participation will receive a comprehensive consent form from the medical team following the clinical consultation. This form comprehensively outlines the nature of the study, what participation entails, and the rights of the participants. The signed document will be retrieved prior to starting COS.

### Additional consent provisions for collection and use of participant data and biological specimens {26b}

Not applicable; data collected in this study will not be used for any ancillary studies.

## Interventions

### Explanation for the choice of comparators {6b}

Patients in the control group will be prescribed their first dose of FSH by the clinician in accordance with standard clinical practice.

Both participating centers adhere to a uniform clinical practice protocol, ensuring consistency in patient treatment and data collection across the trial. In both participating centers, eligible patients will undergo controlled ovarian stimulation, which can be induced with either recombinant FSH (Gonal®, Merck-Serono, Spain; Bemfola®, Gedeon Richter Iberica, Spain) or highly purified human menopausal gonadotropin or hMG (Menopur®, Ferring, Spain; Meriofert®; IBSA; Spain). The first dose of FSH, administered on the second day of the menstrual cycle, is routinely determined by expert physicians for specific patients depending on their age, ovarian reserve markers (AMH levels, AFC), and BMI. Pituitary inhibition will be performed with a GnRH antagonist (Orgalutran®, Organon, Netherlands), and ovulation will be triggered when $$\ge$$ 3 follicles of $$\ge$$ 17 mm diameter are observed, using 250 mcg of choriogonadotropin alfa (Ovitrelle®; Merck-Serono, Spain) or 0.3 mg of Triptorelin (Decapeptyl®, Ipsen Pharma, France) in cases with a risk of OHSS. Following oocyte retrieval, the sperm sample will be prepared for conventional IVF and/or ICSI. Fertilized oocytes will be cultured in vitro and transferred either fresh or frozen. The preferred clinical strategy is single embryo transfer on day 5 of embryonic development, although double embryo transfer and/or day 3 embryo transfer may be performed in specific cases.

### Intervention description {11a}

Patients in the intervention arm will be prescribed the first dose of FSH by IDoser that will take into account the age of the patient, BMI, AFC, and AMH. These data will be retrieved from the patient’s clinical file after their first visit to the clinic, after providing the patient with informed consent documentation.

### Criteria for discontinuing or modifying allocated interventions {11b}

Participants can withdraw from the study at any time and for any reason or no reason. The reason for withdrawal will be recorded if patients choose to disclose this information. Failure to administer the allocated FSH dose and discontinuation of IVF/ICSI for medical reasons will also result in withdrawal. Participants will be informed immediately regarding their withdrawal from the trial, if either an error in dose administration is detected or for a medical reason. If an error in FSH administration or medical reason is detected, the participant’s treatment will be interrupted or allowed to continue based on the clinical judgment of the healthcare provider. The data of withdrawn patients obtained during their participation in the study will be included in the study analysis. Withdrawn patients will not be replaced.

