### Outcomes {12}

The primary efficacy criterion will be the number of mature, MII oocytes retrieved at OPU. This treatment outcome is the closest to the intervention and has a clear impact on IVF/ICSI cycle success. Secondary efficacy endpoints will include cycle cancelations (due to poor response or in the event that no mature oocytes are retrieved), OHSS risk, clinical pregnancy, and live birth per first transfer.

The following variables will be analyzed:Demographic variablesAge of the patient (years)AFCBMI (kg/m$$^2$$)AMH (ng/ml)Center of treatmentCOS outcome variablesNumber of MII oocytesNumber of cumulus-oocyte complexes (COCs)Estradiol at last ultrasound assessment (pg/ml)Number of follicles $$\ge$$ 11mm at last ultrasound checkOHSS risk ([yes/no]; risk is considered as present if estradiol > 5000 pg/ml and or $$\ge$$ 18 follicles $$\ge$$ 11mm at last ultrasound check)OPU cancelation ([yes/no]; present if COS is stopped prior to OPU)Cycle cancelation ([yes/no]; present if no MII oocytes are retrieved at OPU)Pregnancy outcome variablesClinical pregnancy ([yes/no]; present if positive fetal heart beat is observed at 7th week of gestation) per first embryo transferLive birth per first embryo transfer ([yes/no])

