**Assessments:**							
***Baseline variables***	✕	✕					
***Outcome variables***				✕	✕	✕	✕

A detailed description of the timepoints reflected in the figure is as follows:$$-t_1$$: First appointment with the clinician where information on IVF/ICSI treatment is relayed to the patient. Information on the trial is communicated to the patient, and informed consent documentation is handed over to eligible patients. If any of the baseline variables needed for IDoser to function (age, BMI, AFC, and AMH) are not available at this time, steps are put in place to obtain relevant information for the next appointment. These can include petition of blood tests for AMH level results, or echography for AFC assessment.$$t_0$$: Appointment with the clinician where the signed informed consent form is retrieved. Patient is included if all baseline variables are available. Once included, the participant is allocated to either the IDoser FSH selection group or control group. The FSH dose is prescribed to the participant.$$t_1$$: First day of the COS protocol. Participant will self-administer the prescribed dose of FSH.$$t_2$$: Last ultrasound appointment prior to OPU. First outcome variables are registered (OHSS risk and OPU cancelation).$$t_3$$: Day of OPU. Further outcome variables are registered (number of COCs recovered, number of MII recovered and cancelation after OPU).$$t_4$$: Appointment to evaluate the presence of a fetal heart beat at the 7th week of gestation to establish whether pregnancy is achieved after first embryo transfer in current IVF/ICSI cycle. Presence or absence of clinical pregnancy is registered.$$t_5$$: End of study, considered after outcome on live birth after first embryo transfer is obtained. Presence or absence of live birth achieved is registered.Baseline variables include all necessary variables required for IDoser, including age of the patient, BMI, AFC, and AMH levels.

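### A first-dose error or a medical stop counts as leaving the trial, so an MII count can go uncollected and a medically stopped stimulation has no stated status as OPU cancelation

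*Protocol article*

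**What the plan says.** All references are to the protocol article.

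- **Criteria for discontinuing or modifying allocated interventions {11b}.** "Failure to administer the allocated FSH dose and discontinuation of IVF/ICSI for medical reasons will also result in withdrawal". This means leaving the trial, and promptly: "Participants will be informed immediately regarding their withdrawal from the trial, if either an error in dose administration is detected or for a medical reason". Treatment itself need not stop: "the participant’s treatment will be interrupted or allowed to continue based on the clinical judgment of the healthcare provider". On data: "The data of withdrawn patients obtained during their participation in the study will be included in the study analysis". And: "Withdrawn patients will not be replaced".
- **Non-adherence and missing data {20c}.** A participant who did not get the planned intervention is again treated as withdrawn, and the approach is named per-protocol.
- **Outcomes {12}.** "The primary efficacy criterion will be the number of mature, MII oocytes retrieved at OPU". Also: "Secondary efficacy endpoints will include cycle cancelations (due to poor response or in the event that no mature oocytes are retrieved), OHSS risk". Two variables are defined separately: OPU cancelation (stimulation halted before OPU) and cycle cancelation (OPU done, no MII obtained).
- **Participant timeline {13}.** The first dose is taken at t1. At t2, the last ultrasound: "First outcome variables are registered (OHSS risk and OPU cancelation". COC and MII counts and cancelation after OPU are registered at t3, clinical pregnancy at t4 and live birth at t5.
- **Strategies to improve adherence {11c}.** A study nurse verifies the first dose. The team undertakes in general terms to follow patients for outcome data, which are held in the routine electronic record. Withdrawn women are not mentioned.

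**The concern.** The rule does not separate departing from or stopping treatment from leaving the trial. This concerns what is collected, which comes before any choice of analysis set.

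Two problems follow. First, a dose error happens before any outcome is registered. If participation ends there, nothing later falls inside it, although the woman may go on to OPU and have an MII count in her clinic record. Second, a medical stop of stimulation before OPU satisfies the definition of a trial outcome and also triggers withdrawal, and no sentence says that it is counted as the outcome.

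The first FSH dose is the randomised intervention, and response to it could plausibly lead to a medical stop. Loss after randomisation may therefore depend on arm. In a non-inferiority trial, leaving out failed cycles can make two arms look alike when they are not.

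**Working it through.** **1. The plan's own figure.** Inputs from Sample size {14}: margin 2 MII, SD 5.84, one-sided alpha 0.05, power 0.80, drop-out 10%. With a true difference of zero:

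n = 2 × [5.84 × (1.645 + 0.842) / 2]² = 105.4, so 106 evaluable per arm.

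106 / 0.90 = 117.8, so 118 per arm and 236 in total. This reproduces the stated size. The allowance is 118 − 106 = 12 women per arm. The article does not say whether it covers dose errors and medical stops.

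**2. Trigger against time of registration.**

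- *First-dose error:* arises at t1. OHSS risk and OPU cancelation (t2), MII and COC (t3), pregnancy (t4) and live birth (t5) all come later. If withdrawal takes effect on detection at t1, no outcome falls within participation, although {11b} allows treatment to go on.
- *Medical stop before OPU:* this meets the {12} definition of OPU cancelation and the {11b} definition of withdrawal. The stop occurs while she is still a participant, so {11b} may keep it. The text does not say so.
- *OPU with no MII:* registered at t3 with a count of zero. The rule does not affect it.

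**3. Power if MII counts are missing.** With m evaluable per arm and a true difference of zero, power = Φ(2 / [5.84 × √(2/m)] − 1.645).

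- 0% loss, m = 118: 83.8%
- 10% loss, m = 106.2: about 80%
- 15% loss, m = 100.3: 78.2%
- 20% loss, m = 94.4: about 76%

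Lost precision is a modest cost.

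**4. Possible bias, on assumed values.** The documents give no rates of stopped cycles and no mean MII. Suppose that women reaching OPU have the same mean M in both arms, and that the proportion of stopped cycles is higher by e in the IDoser arm. Women with an MII count then show a difference of 0. If a stopped cycle is counted as 0 MII, the difference among all randomised women is −M × e.

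- e = 0: no difference for any M.
- e = 0.05: −0.35 (M = 7) to −0.55 (M = 11).
- e = 0.10: −0.70 (M = 7), −0.90 (M = 9), −1.10 (M = 11).

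To reach the margin of 2 by this route alone, e would have to be 2/M: 28.6% (M = 7), 22.2% (M = 9) or 18.2% (M = 11).

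For M = 9 with 5% stopped in control and 15% in IDoser, a normal approximation with SD held at 5.84 gives these chances of declaring non-inferiority:

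- Women with a count only (112.1 and 100.3): SE = 5.84 × √(1/112.1 + 1/100.3) = 0.803; Φ(2/0.803 − 1.645) = about 80%.
- All women, stopped cycle = 0: SE = 5.84 × √(2/118) = 0.760; Φ(1.10/0.760 − 1.645) = about 42%.

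This shows only what unequal loss could do. It is not an estimate for this trial.

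**The case against.** The strongest reply is that no sentence says data collection stops. {11b} keeps what was obtained before withdrawal, {11c} undertakes to retrieve outcomes, and those outcomes sit in the routine record. On that reading, a medical stop is registered as OPU cancelation and the woman is also listed as withdrawn; the two labels need not conflict. This stands in part. That collection ends is an inference from the withdrawal being from the trial and from the limit on which data are analysed.

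A reader might go further and infer that cancelation and OHSS-risk events are lost, so that a safety difference between arms could vanish. The documents do not support that. The stop happens during participation and its data may be kept, medical reasons are not defined, and poor response is itself named as a reason for the cancelation endpoint.

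A reader might also infer that dose-related withdrawals will gather in the IDoser arm, because there any departure from the model's dose is a failure to give the allocated one. This is conceivable but not shown. Women in both arms self-administer, a nurse checks each dose, and no clinician override of the model is described.

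Finally, under the per-protocol approach of {20c}, women with a dose error would be set aside even if followed. That does not answer the point: an analysis of all randomised women, in this plan or a later one, needs outcomes that the withdrawal rule, read as written, does not require anyone to collect.

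**Conclusion.** The point holds in a limited form. Read as written, {11b} and {20c} leave a woman with a first-dose error without a primary outcome even when she reaches OPU, and the general follow-up promise in {11c} does not say that it covers her. A medical stop of stimulation before OPU is both an endpoint event and a withdrawal, and the text should say that it is counted; its loss is possible, not certain. Cycle cancelation with no MII at OPU is unaffected.

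The size cannot be fixed from the documents. If losses stay within 10%, power is about 80%; at 20% it is about 76%. The larger risk is bias, which arises only if loss differs between arms or is related to outcome. Under the assumed excesses of 0 to 10 percentage points and means of 7 to 11 MII, the hidden deficit runs from 0 to 1.1 MII, against a margin of 2. These figures also assume that a stopped cycle counts as 0 MII. That value may be set in an analysis plan not seen here, and its absence from the article is not part of this point.

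**What to change.** Reword {11b} and {20c} so that:

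- only withdrawal of consent ends data collection;
- a wrong or missed first dose is recorded as a protocol deviation;
- a medical stop of stimulation before OPU is counted as OPU cancelation, with its reason;
- MII, COC, OHSS risk, cancelation, pregnancy and live birth continue to be taken from the routine record for every randomised woman.

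Reconcile {11b}, which includes withdrawn women's data in the analysis, with {20c}, which describes a per-protocol strategy restricted to adherent participants. Whether treatment continues remains the clinician's decision, as now.

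The cost is a wording amendment, with the ethics committee and authority approval that the article already requires for amendments, and minor extra data retrieval. No added visits are needed, since {11c} and {18a} place these outcomes in routine care. The planned 118 per arm does not change.
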